### Randomization and blinding

The study is a two-center, double-blind, and placebo-controlled trial. With the block randomization method, the random number table will be generated by an independent third party, the Hospital’s Clinical Evaluation Center, using SAS 9.4 software (SAS Institute, Cary, NC, USA). The randomized assignment sequence is placed in a sealed opaque envelope whereas the blind codes are kept at the department of research management and can be reproduced when needed. All of the patients participated in this study; principal investigators and research staff will remain blinded to all patients’ randomization assignments throughout the duration of this study. Eligible patients will be randomly allocated to either the acupuncture or sham group according to a 1:1 ratio.

### Intervention

All participants will receive either real acupuncture or sham acupuncture for 8 weeks. The frequency of acupuncture intervention is three times per week for the first 4 weeks and twice a week for the following 4 weeks. Every participant will be placed in a separate room to receive the treatment for 30 mins every time. All acupuncturists participating in the study are licensed medical practitioners to ensure the accuracy and consistency of the treatments provided. Meanwhile, adverse reactions that may occur during the study will be recorded.

### Acupoints and needles

Acupoints include three on the head, four on the back, two on the upper extremities, and eight on the lower extremities. Before acupuncture treatment, a small pad will be pasted on each acupoint. All the needles will be inserted in the acupoints through these pads (Fig. 1).

**Fig. 1 Fig1:**
[figure not shown]
The comparison of acupuncture treatment and sham acupuncture. **a** real acupuncture. **b** sham acupuncture.1. Needle handle. 2. Needle body. 3. Adhesive pad. 4. Skin. 5.Sharp tip. 6. Blunt tip. Needles: Both real and sham needles (Shanghai Zhenkang Medical Technology Company, Ltd., Shanghai, China) are stainless-steel needles, which have the same size of 0.30 × 40 mm according to the depth of acupoints’ site in this trial

### Description of sham acupuncture

The sham needle consists of a needle with a blunt tip and a circle adhesive pad (Fig. 1). The needle is very similar to the real needle, 0.30 mm wide, and 40 mm long. The adhesive pad is made of the sterile cylindrical polyethylene foam (10 mm in diameter and 5 mm in length) with a double-sided adhesive tape at the bottom. The adhesive pad supports the sham needle on the acupoint and ensures the implementation of blinding during the intervention. Thus, the sham needle with a blunt tip only contacts the skin surface but will not penetrate into the skin of the participants during sham acupuncture.

### Process of the treatment

Each participant will be interviewed by an investigator prior to the commence of treatment and fill out the CRF with a series of initial data at baseline of the study. After skin sterilization, an adhesive pad made of aseptic cylindrical polyethylene foam with double-sided tape on the bottom is placed on the acupuncture points for fixing the needle and implementation of blinding. The points and manipulation of acupuncture in both groups are the same, with Baihui (DU20), bilateral Tianzhu (BL10), bilateral Jianjing (GB21), bilateral Quyuan (SI13), bilateral Shousanli (LI10), Ququan (LR8), and bilateral Taichong (LR3) with even method, bilateral Sanyinjiao (SP6), Zusanli (ST36) with reinforcing method (Fig. 2). Needles will be retained for 30 min during treatment. Following needle insertion, the state of “de qi” (feelings of patients including soreness, numbness, heaviness, or tingle at the points) is achieved by twirling, lifting, and thrusting, which is essential for the effective treatment [17].

**Fig. 2 Fig2:**
[figure not shown]
The accupoints adopted in the study and their indications

### Combination therapy

#### Drugs allowed to be combined

▪ Chinese medicine including traditional Chinese medicine decoction and Chinese patent medicine) used for at least 2 weeks with stable dosage and type;▪ Drugs for cardiovascular and cerebrovascular diseases and the like used for at least 6 months with stable dosage and type;▪ All the combined medications are required to be recorded with detailed information.

#### Drugs not allowed to be combined

▪ Non-steroidal anti-inflammatory drugs;▪ Oral corticosteroids;▪ Opioid analgesics.

### Outcome measurements

#### Primary outcomes

The visual analogue scale (VAS) [18] for pain intensity: Using a horizontal ruler of 100 mm, “0” representing no pain and “100” representing unbearable pain. The pain VAS intensity will be measured at the baseline, week 4, week 8. A total of seven assessments will be measured monthly during the 8-week treatment period and the follow-up period at week 12, 16, 20, and 24.Revised Fibromyalgia Impact Questionnaire (FIQR) [19] for pain intensity: FIQR assesses the health status of patients with fibromyalgia, including physical function, working condition, depression, anxiety, pain, stiffness, fatigue, sensitivity, and well-being. The scoring system ranges from 0 to 100, in which a higher score represents a heavier state of FM. Each subject will be asked to complete the questionnaire before treatment based on the overall situation of the past 24 h [20].

#### Secondary outcomes

Multidimensional Assessment of Fatigue scale (MAF): The MAF scale covers 16 items that measure five dimensions of fatigue: degree, severity, distress, degree of interference with activities of daily living, and timing. Items 1–14 contain ten-point numerical rating scales and items 15–16 have multiple-choice responses. The ten-point numerical rating scale ranges from 1 to 10 [21].The MOS 36-item short-form health survey (SF-36): It is a comprehensive scale reflecting the quality of life containing contents of eight domains: physical functioning, role-physical, bodily pain, general health, vitality, social functioning, role-emotional, and mental health. Moreover, it has an independent item reporting health transition during the past 1 week [22].Beck Depression Inventory (BDI) [23]: The scale was used to assess the severity of depressive symptoms. It contains 21 entries, each of which is scored from 0 to 3. The scale is divided into a total score of 21 items. The severity of depression is divided into four degrees by the total score. The total score between 0 to 13 represents no depression, 14 to 19 mild depression, 20 to 28 moderate depression, and 29 to 63 severe depression.Pittsburgh Sleep Quality Index (PSQI) [24]: It consists of subjective sleep quality, sleep time, sleep efficiency, sleep disturbance, whether or not to use hypnotic drugs and effects on daytime function. It has a total of seven items, with score 0–3 for each. The higher the cumulative score, the worse the quality of sleep.Chinese perceived stress scale (pss-14): This scale is to assess the patient’s personal feelings and thoughts in the past month. It consists of 14 items that each item has six response options ranging from “All of the time” to “None of the time” [25].Changes in the number of 18 tender points: The pressure applied to each tender point was 4 kg/cm^2^ [26]. The patients will be asked to inform the investigators when tenderness occurred while the total number will be calculated and compared to the baseline.Patient satisfaction for the treatment: Patient satisfaction will be assessed by Patient Global Impression of Change (PGIC) [27] after 8 weeks of treatment, which is a PRO counterpart to the clinical assessment by doctors. It consists of one item taken from the Clinical Global Impressions scale (CGI) and adapted to the patient. The levels of satisfaction will be measured with seven scales ranked from 1 to 7, 1 is for “Very much improved” and 7 for “Very much worse”.

Adverse events will be monitored during the 8 weeks of treatment. Any adverse reactions occurred during the study will be documented in the “Adverse Reaction Form” while the patients are followed up until the symptoms disappear or the abnormal indicators return to normal. In the event of a serious adverse event, the necessary measures will be taken immediately for the safety of the subject.

Primary and secondary efficacy indicators will be evaluated every 4 weeks except the PGIC assessed after 8 weeks of treatment. Safety evaluations will be conducted at baseline and week 8 including blood pressure, breathing, heart rate, blood routine, urine routine, liver, and kidney function (ALT, AST, Cr, BUN), Electrocardiogram (Figs. 3 and 4).

**Fig. 3 Fig3:**
[figure not shown]
Trial flow and study design. General information = name, gender, age, height, weight, duration of illness, smoking history, drinking history, education, job, family income. 1st outcome = pain-VAS, Revised Fibromyalgia Impact Questionnaire (FIQR). 2nd outcome = Multidimensional Assessment of Fatigue scale (MAF), SF-36, pss-14, Beck Depression Inventory (BDI), Pittsburgh Sleep Quality Index (PSQI), changes in the number of 18 tender points. 3rd outcome = Patient satisfaction for the treatment (PGIC)

**Fig. 4 Fig4:**
[figure not shown]
SPIRIT figure of enrolment, interventions, and assessments. *FIQR* Revised Fibromyalgia Impact Questionnaire, *MAF* Multidimensional Assessment of Fatigue scale, *SF-36* The MOS 36-item short-form health survey, *pss-14* Chinese perceived stress scale, *BDI* Beck Depression Inventory, *PSQI* Pittsburgh Sleep Quality Index, *PGIC* Patient satisfaction for the treatment

### Sample size

The calculation for sample size was based on the changes in pain VAS scores. We adopted the method described in previous studies [28, 29] that the changes are − 4.00 in the acupuncture group and − 2.50 in the sham-acupuncture group, respectively, indicating that the mean difference between two group is 1.5 with standard deviations of 2.55 and 1.25. Given that the ratio of the acupuncture group and the control group is 1:1, the required sample size is 29 cases for each group as estimated by SAS 9.4 software using a two-sided test with a significance level (α) of 0.05 and a power (1-β) of 0.80. With a possible dropout rate of around 15%, the acupuncture group and control group require a total of 68 cases.

### Quality control

The standard operation procedure (SOP) for the acupuncture operation method is established. The identification, registration, and treatment of participants will be managed by the SOP. Training of acupuncture theory and surgical aseptic operation for acupuncturist with certain clinical experience will be conducted to ensure the consistency of repeated operations of acupuncture. A corresponding data security monitoring plan will be developed. All adverse events are recorded in detail, properly processed, and tracked until properly resolved or the condition is stable, and reported to the Ethics Committee in a timely manner.

### Trial monitoring

The Trial Steering Committee is established for monitoring the trial conduct and ensuring the safety and quality of the data, which consists of three members including a senior rheumatologist, an acupuncturist, and a statistician. The committee is independent from the study group and has no conflict of interest with the investigators. They will provide regular supervision and hold monthly meetings (either face to face or online) to ensure that the trial is conducted smoothly and ethically. The committee will also be responsible for monitoring data collection to ensure the authenticity and integrity of the data. They will conduct at least one on-site visit every 6 months during the process of the trial. During the visit, they will interview investigators, examine the original research documents, check the participant enrollment, and confirm the compliance of clinical centers with the trial protocol. Moreover, they will identify the problems in the trial and provide recommendations on the amendment of the protocol. If any decisions on changes of the protocol were to be made, they would notify the funder first. Subsequently, the PI will apply for approval from the Ethics Review Board with written application and notify the investigators with written notice upon receiving the approval from the ethics committee. Any deviations from the protocol will be fully documented using a breach report form. In addition, the protocol will be updated immediately in the clinical trial registry.

### Data management

The data of this clinical trial is managed by Beijing CreateMed Medicine Technology Co., LTD, which ensures the authenticity, integrity, and privacy of clinical test data during the research process. The clinical trial database is structured with EpiData 3.1 (Chinese version) by the appointed data manager who is responsible for the regular database management and maintenance. All of the data from the research centers will be imported into the clinical trial database by two research assistants. Any missing or incorrect data will be detected by software system. In such case, the original CRFS will be checked to correct or complete every piece of data.

### Statistical analysis

For statistical analysis, mean ± standard deviation (M ± SD) is used for continuous variables which meet normal distribution. Chi-square or Fisher’s exact test will be performed to compare baseline characteristics for categorical variables. The primary outcome variable between the two groups will be analyzed by Chi-square test or Fisher’s exact test, while the analysis of independent-samples *t* test or Wilcoxon rank-sum test will be used for secondary outcomes.

To assess the effect of acupuncture therapy for fibromyalgia, intention-to-treat (ITT) [30] analysis will be performed for statistical analysis. A value of *P* < 0.05 with two-tailed test will be considered statistically significant.

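### The primary outcomes are continuous 0-100 scores and the trial is sized on a mean difference, but the analysis section assigns them Chi-square or Fisher's exact test without defining a cut-off

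*Protocol article*

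**What the plan says.** Three sections of the protocol article bear on this.

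- **Outcome measurements, Primary outcomes.** There are two primary outcomes, both numeric scores. Pain VAS: "Using a horizontal ruler of 100 mm, “0” representing no pain and “100” representing unbearable pain". FIQR: "The scoring system ranges from 0 to 100, in which a higher score represents a heavier state of FM".
- **Sample size.** "The calculation for sample size was based on the changes in pain VAS scores". The assumed mean changes are -4.00 with acupuncture and -2.50 with sham, so that "the mean difference between two group is 1.5 with standard deviations of 2.55 and 1.25". The calculation uses a "two-sided test with a significance level (α) of 0.05 and a power (1-β) of 0.80" and equal allocation. It arrives at 29 per group, or 68 in total after about 15% dropout.
- **Statistical analysis.** "The primary outcome variable between the two groups will be analyzed by Chi-square test", or by Fisher's exact test. In the same sentence the independent-samples t test or "Wilcoxon rank-sum test will be used for secondary outcomes".

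No section turns VAS or FIQR into categories. The article gives no responder definition, cut-off or expected response rate.

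**The concern.** Chi-square and Fisher's exact tests compare proportions. Applied to a 0-100 score they need a dichotomy, and the article supplies none. Once a dichotomy is imposed, the hypothesis is about the share of patients beyond a threshold, not the 1.5-point mean difference used for sizing.

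Two things are at stake. The confirmatory test cannot be run from the article as it stands, because an essential element is left open. And the 80% power belongs to a different analysis, so a reader cannot tell what power the named test has.

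This is more than detail left to an analysis plan. The article names a test, assigns it to the primary outcome and contrasts it with the tests for secondary outcomes. A separate sentence already gives Chi-square and Fisher to categorical baseline variables, so this one cannot be read as referring to those. A later plan that compared means would have to contradict the published text.

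**Working it through.** **Inputs from the Sample size section:** mean changes 4.00 and 2.50 (as improvements), difference 1.5, SDs 2.55 and 1.25, two-sided α 0.05, power 0.80, 1:1 allocation, 29 per group.

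**Assumptions, not in the article:** VAS change is normal; the 1.5 is on a 0-10 scale (the exclusion criteria give VAS in cm out of 10, the outcome section in mm out of 100); a responder is a patient whose improvement reaches a cut-off c.

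**Step 1. Reproduce the plan's figure as a comparison of means.**
- Pooled SD = √[(2.55² + 1.25²)/2] = √(8.065/2) = 2.008.
- n per group = 2 × [2.008 × (1.960 + 0.842)/1.5]² = 28.1, rounded up to 29.
- Standard error at n = 29: √(8.065/29) = 0.527. Noncentrality: 1.5/0.527 = 2.84.
- Power: 81.2% (normal approximation), 79.8% (pooled t), 79.3% (Welch t).
- Dropout: 58/0.85 = 68.2, against 68 stated.

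So 29 per group and 80% power hold for a comparison of means, up to rounding.

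**Step 2. Power of the named test.** Response probabilities are Φ((4.00 − c)/2.55) with acupuncture and Φ((2.50 − c)/1.25) with sham. For c = 4 these are Φ(0) = 0.500 and Φ(−1.2) = 0.115. Power is the summed binomial probability, over all possible 2×2 tables with 29 per arm, of those with P < 0.05 (uncorrected Chi-square, or Fisher).

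| Cut-off c | Acupuncture | Sham | Chi-square power | Fisher power |
|---|---|---|---|---|
| 1.0 | 0.880 | 0.885 | 5.5% | 1.2% |
| 2.0 | 0.784 | 0.655 | 18.6% | 12.3% |
| 2.5 | 0.722 | 0.500 | 39.8% | 30.1% |
| 3.0 | 0.653 | 0.345 | 65.8% | 55.3% |
| 3.5 | 0.578 | 0.212 | 82.5% | 74.7% |
| 4.0 | 0.500 | 0.115 | 91.4% | 86.3% |
| 4.5 | 0.422 | 0.055 | 94.6% | 89.9% |
| 5.0 | 0.347 | 0.023 | 95.7% | 88.2% |
| 5.5 | 0.278 | 0.008 | 94.5% | 79.5% |
| 6.0 | 0.216 | 0.003 | 88.0% | 59.7% |

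The best values on a finer grid are 95.7% for Chi-square (c = 5.05) and 90.0% for Fisher (c = 4.6).

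The row for c = 1 shows that the named test addresses a different quantity: the full 1.5-point mean difference is present, yet the response rates are almost equal. The high power at large cut-offs owes much to the acupuncture SD being about twice the sham SD (2.55/1.25 = 2.04), which leaves hardly any sham responders.

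**Step 3. Sensitivity to the SDs.** With a common SD of 2.008 in both arms (an assumption; the article gives unequal SDs), the best power at any cut-off from 1 to 6 is 60.7% for Chi-square and 50.0% for Fisher, both at c = 3.25.

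**The case against.** **Power is not shown to be below 80%.** A reader might infer from the mismatch that the trial lacks its stated power. The documents do not support that. With the plan's own SDs, Chi-square power is at least 80% for cut-offs of about 3.5 to 6, and Fisher power is above 80% at 4, 4.5 and 5. Only the common-SD scenario stays below 80% throughout, and it is not the plan's. This objection stands: the most that can be said is that the 80% does not carry over and that the named test's power is undefined.

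**A cut-off need not be post hoc.** A reader might also infer that the threshold would be chosen after seeing the data. A responder definition could sit in the full protocol or analysis plan, neither of which is shown. This stands too: the article defines none, and nothing further follows about intent or timing.

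**It may be a slip of the pen.** Suitable tests for continuous scores appear in the same sentence, so the primary and secondary assignments may simply have been swapped. That is plausible but cannot be established from the text. It supports a small correction and does not remove the need for one.

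None of this resolves the conflict between the Sample size and Statistical analysis sections.

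**Conclusion.** The point holds as a contradiction within the article, and it concerns the confirmatory test. The article defines two continuous primary scores and sizes the trial on a mean difference, then assigns a test for proportions to the primary outcome without a cut-off.

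The size of the consequence is an indeterminacy, not a demonstrated loss. Depending on the unstated cut-off, the named test's power could lie almost anywhere between the significance level and well above the target. The range in the working rests on normal changes, the plan's SDs, a 0-10 scale and 29 evaluable patients per arm. The contradiction itself rests on no assumption.

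**What to change.** Rewrite the sentence in Statistical analysis to state that:

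- both primary scores, change in pain VAS and FIQR, are compared between arms as continuous variables, using the t test or Wilcoxon test already named or, preferably, a baseline-adjusted linear model;
- the mean difference, its 95% CI and the two-sided P value are reported;
- Chi-square and Fisher's exact tests are used only for categorical variables.

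FIQR keeps its place as a primary outcome. Any responder analysis should be supportive, with its cut-off fixed before unblinding. The sponsor should also confirm the primary time point, since the outcome section lists seven assessments and singles out none. Week 8, the end of treatment, is a suggestion only.

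If a responder comparison really is the intended primary analysis, the article must instead state the cut-off and expected response rates and redo the sample size for proportions.

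The preferred change costs a few lines of text, with no patients and no new data; the 29 per group already computed remains valid. The article gives no database lock date, so the correction should be made, dated and recorded before unblinding.

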## Methods

### Study design

This study is a two-center, blinding, randomized, controlled trial with two arms for 8 weeks. A total number of 68 patients with FM who meet the criteria are randomly divided into acupuncture group and sham acupuncture group according to the ratio of 1:1. The intervention will be performed for 8 weeks with a follow-up of 16 weeks. The treatment of acupuncture and placebo is three times a week for the first 4 weeks and twice a week for the next 4 weeks. This clinical trial will be completed at Guang’anmen Hospital of China Academy of Chinese Medical Sciences and Shenzhen Traditional Chinese Medicine Hospital. This study will follow the relevant regulations of the World Medical Congress “Helsinki Declaration” and has been approved by the Ethics Committee of Guang’anmen Hospital and Shenzhen Traditional Chinese Medicine Hospital. All enrolled subjects will be informed with a complete and comprehensive introduction including the purpose, procedure, and possible risks of the study. The informed consent will be obtained before the start of this study.

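### The between-arm tests named are all unadjusted two-sample tests, so baseline, centre and the repeated visits are not used as they could be, at some cost in precision in a small trial

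*Protocol article*

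**What the plan says.** The Statistical analysis section names the tests. For the primary outcome: "The primary outcome variable between the two groups will be analyzed by Chi-square test or Fisher’s exact test". For the secondary outcomes it names an independent-samples t test or, in its words, "Wilcoxon rank-sum test will be used for secondary outcomes". It also states that "intention-to-treat (ITT) [30] analysis will be performed for statistical analysis". It mentions no covariate, no centre term and no method for repeated measurements.

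The design collects more than these tests use:

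- **Centres.** Study design: "This study is a two-center, blinding, randomized, controlled trial with two arms for 8 weeks". The Discussion places the centres in Beijing and Shenzhen.
- **Visits.** Under Primary outcomes, pain VAS is assessed seven times: at baseline and at weeks 4, 8, 12, 16, 20 and 24. The text after Secondary outcomes puts the primary and secondary efficacy measures on the same 4-weekly schedule, except PGIC, which is taken once after 8 weeks.
- **Randomisation.** "With the block randomization method, the random number table will be generated by an independent third party". Stratification by centre is not mentioned.
- **Size.** The Sample size section works from changes in pain VAS: "mean difference between two group is 1.5 with standard deviations of 2.55 and 1.25", with a "two-sided test with a significance level (α) of 0.05 and a power (1-β) of 0.80". This gives 29 per group, raised to 68 in total for dropout.

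**The concern.** The analysis method is stated in the article, so this is a choice that can be judged and not a gap. A two-sample test at one visit leaves the baseline value unused, or uses it only by subtraction. It also sets aside centre and the other visits. Pain at baseline usually predicts later pain to some degree, and adjusting for it removes that part of the residual variance and corrects for chance imbalance between arms at baseline.

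The trial has little precision to spare. It is sized for 80% power with 29 evaluable patients per arm, and the Discussion itself lists limited sample size as a limitation. At stake is a wider confidence interval than the collected data require. The type I error rate is not in question.

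**Working it through.** **Inputs from the Sample size section.** Difference in mean change d = 1.5; SDs 2.55 and 1.25; two-sided α = 0.05; power 0.80; n = 29 per arm.

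**Inputs not in the documents, so assumed.** Correlation r between baseline and follow-up pain VAS: 0.3, 0.5, 0.7. Ratio k = baseline SD / follow-up SD: 1, 0.8, 0.6. Values of k below 1 are considered because the Exclusion criteria remove patients with a pain VAS below 4 on a 10 cm scale, which cuts off the lower part of the baseline distribution but not of the follow-up distribution.

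**Step 1: reproduce the plan's figure.** Root-mean-square SD = √((2.55² + 1.25²)/2) = 2.008. Normal approximation: n = 2 × (2.008 × (1.960 + 0.842)/1.5)² = 28.13, rounded up to 29 per arm. The plan's 29 is reproduced.

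**Step 2: reference power.** For a pooled t test on change with 29 per arm, SE = 2.008 × √(2/29) = 0.527 and the noncentrality is 1.5/0.527 = 2.84. On 56 degrees of freedom the power is 0.798. (The normal approximation gives 0.812.)

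**Step 3: variance of ANCOVA relative to a change-score comparison.** Taking the follow-up SD as 1 and the baseline SD as k, the change has variance 1 + k² − 2rk, and the follow-up value adjusted for baseline has variance 1 − r². The ratio is

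f = (1 − r²) / (1 + k² − 2rk).

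With k = 1 this reduces to (1 + r)/2. It never exceeds 1, because the denominator minus the numerator equals (k − r)².

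**Step 4: power with ANCOVA.** Put SE = 0.527 × √f, with d = 1.5 and 29 per arm as before:

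| k | r = 0.3 | r = 0.5 | r = 0.7 |
|---|---|---|---|
| 1.0 | f = 0.65, power 0.93 | f = 0.75, power 0.90 | f = 0.85, power 0.86 |
| 0.8 | f = 0.78, power 0.88 | f = 0.89, power 0.84 | f = 0.98, power 0.81 |
| 0.6 | f = 0.91, power 0.83 | f = 0.99, power 0.80 | f = 0.98, power 0.81 |

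Example for k = 0.8, r = 0.3: f = (1 − 0.09)/(1 + 0.64 − 0.48) = 0.91/1.16 = 0.78; SE = 0.527 × √0.78 = 0.467; noncentrality 1.5/0.467 = 3.21; power 0.88.

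In terms of patients, the k = 1 row is worth 29/f = 45, 39 and 34 per arm analysed by change score. At k = 0.6 it is worth 32, 29 and 30, which for r = 0.5 and 0.7 is almost nothing.

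**What this does not include.** Any further gain from the centre term or from modelling all visits together cannot be computed from the documents. The calculation treats r and k as the same in both arms and uses the pooled SD, although the two SDs differ. One degree of freedom for the covariate makes no visible difference at this size.

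**The case against.** The strongest reply is that nothing here is an error. Randomisation makes unadjusted tests valid, and ANCOVA or a mixed model is one reasonable choice among several. That stands, and it limits the point to efficiency.

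A second reply is that baseline is not ignored. The Sample size section works on change in pain VAS, and under Secondary outcomes the tender-point count is compared with baseline. This also stands. The calculation therefore takes the change-score t test as its reference, which credits the plan with using baseline by subtraction. That credit is generous for the primary outcome, where the section names a categorical test; this is a separate fault and none of the gain above is drawn from it.

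A third reply is that the size of the gain depends on quantities nobody has stated. It does: equal SDs are the favourable case, and with a restricted baseline the gain can vanish.

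A reader might infer more than the article supports:

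- **That patients with a missing visit are dropped, so that intention-to-treat becomes a complete-case analysis.** The article commits to intention-to-treat, excludes nobody and is silent on missing values. A two-sample test can be run on imputed data, and an article may leave that rule to an analysis plan that is not shown. The allowance of about 15% for dropout already covers the planned loss: 34 × 0.85 = 28.9 per arm.
- **That arms may well be unbalanced within centre.** Any figure for this would need the number of patients per centre and a list without blocks. The article gives no centre sizes and does specify block randomisation.
- **That leaving out centre ignores a design factor.** No stratification by centre is described, so none is being ignored.

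**Conclusion.** The point holds as a loss of precision. The tests named use neither a baseline covariate, nor centre, nor the repeated visits, although the data for all three are collected for every efficacy scale except PGIC. For pain VAS, replacing a change-score t test by baseline-adjusted ANCOVA would raise power from 0.80 to between 0.86 and 0.93 if baseline and follow-up SDs are equal and r lies between 0.7 and 0.3. With a baseline SD of 0.6 to 0.8 of the follow-up SD, power would be about 0.80 to 0.88. The direction is safe, since under this model the variance ratio cannot exceed 1. The size is uncertain and may be negligible, because r and k are assumptions. The documents do not support a charge of invalid tests, of broken intention-to-treat or of a quantified centre imbalance.

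**What to change.** In the Statistical analysis section, state that pain VAS, FIQR and the other continuous scales (not PGIC) are analysed as continuous outcomes, in one of two ways:

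- ANCOVA of the week-8 value on arm, with the baseline value and centre as covariates; or
- a mixed model for repeated measures over the post-baseline visits, with arm, visit, arm-by-visit, baseline value and centre, reporting the week-8 arm contrast.

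Report the adjusted mean difference with its 95% confidence interval. PGIC has no baseline and can keep a two-sample test.

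The cost is a few lines of analysis wording and slightly more programming. No extra patients, visits or measurements are needed.
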